#### Quantitative data collection and analysis

Data relating to progression criteria (e.g. recruitment and retention rates) will be collected throughout. Quantitative data will be collected from patients through postal questionnaires, once they have provided informed consent, at baseline and at 4 and 8 months after practice randomisation (Additional file 3). Prescribing data will be collected by research nurses from practice record systems and will be based on a data collection tool developed and pilot tested in advance (Additional file 3). An intention to treat analysis will be conducted, with data from all eligible patients being included in analyses. We will determine the estimates of the variability in secondary outcomes (e.g. treatment burden and health-related quality of life; potentially inappropriate prescribing, number of prescribed medications and rates of deprescribing; and completion of medication reviews) at baseline and/or study end, the variability in the change in responses over time and the likely proportion of missingness in the responses. Quantitative data will inform the decisions on the number of clusters required, optimal cluster size and potential intracluster correlation for a subsequent definitive trial.

#### Exploratory analysis

Linear and nonlinear mixed-effects models, which account for the cluster design and allow adjustment for baseline measurements, will be used to tentatively explore the differences in the secondary outcomes between the pilot trial arms.

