**Fig. 1 Fig1:**
[figure not shown]
MyComrade study design

A total of 16 practices will be recruited (eight in ROI; eight in NI), and four practices in each jurisdiction will be randomly allocated to the intervention or control arms. Patients with multimorbidity who are prescribed 10 or more repeat prescription medications will be identified in each practice. From each practice, 20 patients with multimorbidity will be recruited, providing a total of 320 participants. The list of 20 consented patients from each practice will be shared with participating GPs/PBPs. In the intervention arm, pairs of GPs/GP and PBPs will use the MyComrade intervention and will be asked to complete collaborative medication reviews before the 4-month follow-up time point. ROI pairs will be GP-GP, and NI pairs will be GP-PBP. Control practices will proceed with usual care. Participant data will be collected from primary care practice records and postal questionnaires sent to participants at baseline before randomisation takes place and at 4 and 8 months after the date of randomisation. Qualitative interviews to assess the study feasibility and acceptability and to explore experiences related to multimorbidity management will be conducted with a purposive sample of GPs and PBPs participating in the study, practice administration staff and patients.

A Public and Patient Involvement group has been established, involving four adults (two women and two men) from both NI and ROI and living with multimorbidity. This group have provided input into the patient recruitment materials, and qualitative interview guides, and will provide input into the interpretation of the qualitative findings and methods for disseminating the study findings. The establishment and running of this group as research partners in this study are guided by the PPI Ignite @ NUI Galway programme office, part of a national PPI programme funded by the Health Research Board in Ireland.

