### Sample size

As this is a pilot study, a formal sample size calculation was not done [38]. This study aims to recruit 16 primary care practices (eight in NI and eight in ROI) and 20 patients per practice (*N* = 320), based on recommendations from Eldridge et al. [20] and the CONSORT guidance [21] on the minimum number of clusters required in pilot and definitive cRCTs, respectively. The aims of this pilot cRCT are to investigate feasibility and acceptability and to identify the most suitable primary outcome(s) for a definitive cluster randomised trial. The estimates from this pilot trial will be used to calculate the sample size needed using the methods outlined by Rutterford et al. [39].

Based on an assessment of the number of practices and practice sizes in the region, we will invite 50 patients per practice and, a priori, have defined a success criterion as 40% of the total number of participants invited to be recruited to the research evaluation (approximately 20 patients per practice).

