### Randomisation

To limit recruitment bias and help ensure that equal numbers of patients will be recruited in both arms of the trial, randomisation of the practices to intervention or control group will take place after patient recruitment has been completed [40]. Practices will be allocated using an online system, called Sealed Envelope, by a biostatistician blinded to allocation. Practices will be allocated by minimisation according to practice size (< 4 or 4+ GPs) in the ratio 1:1.

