There are limitations associated with the proposed design. The study setting encompasses the whole of NI but is limited to the border region of ROI. The two settings differ in terms of characteristics such as the presence of major urban centres, which has an impact on the characteristics of GP practices that can be recruited and the number of practices available to recruit. GP practices in NI and ROI differ in a number of ways including typical practice size, often being larger in NI and practice record and medication coding systems, impacting methods of identification of eligible participants.

The overarching aim of this intervention is to optimise the management of medications prescribed for people living with multimorbidity, specifically those with prescriptions for 10 or more repeat medications. This study is an essential step in examining the potential for MyComrade to achieve this overarching aim. To gain an accurate understanding of the complex issues related to polypharmacy and medicines management in multimorbidity, and produce an effective and implementable intervention, this programme of research has been conducted closely in line with current recommendations. Therefore, this research will contribute to the evidence-base related to intervention development and feasibility testing and the management of multimorbidity in primary care nationally and internationally. The findings will be disseminated to a range of audiences, with guidance from the PPI group, including GPs, PBPs, secondary care providers and the public, through a range of media, including a dissemination event, conferences and publication.

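### The exploratory outcome models name clustering and baseline but not practice size or jurisdiction, the two factors the allocation balances; this matters mainly for outcomes weakly tied to baseline

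*Protocol article*

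**What the plan says.** The allocation is balanced on two things.

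- **Practice size.** Under Randomisation: "Practices will be allocated by minimisation according to practice size (< 4 or 4+ GPs) in the ratio 1:1".
- **Jurisdiction.** Under Trial design, with eight practices in each jurisdiction: "four practices in each jurisdiction will be randomly allocated to the intervention or control arms". The Abstract says the same. Read as four practices per arm in NI and four per arm in ROI, this balances jurisdiction by design, although Randomisation does not list it as a factor.

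The Exploratory analysis section is one sentence on how arm differences in the secondary outcomes will be explored: "Linear and nonlinear mixed-effects models, which account for the cluster design and allow adjustment for baseline measurements, will be used". It neither names practice size or jurisdiction nor rules them out.

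On the use of the variance estimates, Quantitative data collection and analysis says: "Quantitative data will inform the decisions on the number of clusters required, optimal cluster size and potential intracluster correlation for a subsequent definitive trial". Sample size adds that pilot estimates will feed the definitive calculation. Neither section says which model the ICC comes from.

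**The concern.** When allocation is balanced on a prognostic factor that the model omits, the factor's effect cancels out of the estimated arm difference but stays in the between-practice variance. The model then reports more uncertainty than the design has, and the practice random effect counts the factor's effect as intracluster correlation.

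The article gives reasons to expect both factors to be prognostic for some outcomes. Study setting describes different payment systems and pharmacist access in most NI practices. The Discussion cites lower self-reported health in NI in one study, and adds: "GP practices in NI and ROI differ in a number of ways including typical practice size, often being larger in NI".

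The variance estimates have two later uses: planning the size of the definitive trial and choosing its primary outcome. An outcome that differs between the two health systems could look noisier than it would be in a trial that balances and adjusts for jurisdiction.

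**Working it through.** **The plan's own figures.** 16 × 20 = 320 patients, and 0.40 × 50 invited = 20 per practice. Both reproduce. There is no power calculation to reproduce.

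**Inputs.** From the article: 16 practices, m = 20 patients each, 8 practices per arm. Assumed, because the article gives none: within-stratum ICC 0.05, within-stratum total variance 1, mean differences d (NI–ROI) and s (large–small) of 0 to 0.3 SD, and each factor split evenly within each arm.

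**Formulas (analysis of practice means).**
- Variance of a practice mean within strata: v = 0.05 + 0.95/20 = 0.0975.
- Added to the residual mean square when both factors are omitted: a = (16/14) × (d² + s²)/4.
- 95% half-width: t × √(mean square/4). Omitting both factors: v + a on 14 df, t = 2.145. Including both: v on 12 df, t = 2.179.
- ICC with both omitted: (0.05 + a)/(1 + a). Design effect: 1 + 19 × ICC.

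**Case 1: baseline explains little.**

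| d / s (SD) | a | Half-width omitted vs included | Ratio | ICC omitted | Design effect (1.95 if included) |
|---|---|---|---|---|---|
| 0 / 0 | 0 | 0.335 vs 0.340 | 0.98 | 0.050 | 1.95 |
| 0.2 / 0 | 0.0114 | 0.354 vs 0.340 | 1.04 | 0.061 | 2.15 |
| 0.2 / 0.2 | 0.0229 | 0.372 vs 0.340 | 1.09 | 0.071 | 2.35 |
| 0.3 / 0 | 0.0257 | 0.376 vs 0.340 | 1.11 | 0.074 | 2.40 |
| 0.3 / 0.3 | 0.0514 | 0.414 vs 0.340 | 1.22 | 0.096 | 2.83 |

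A simulation of 4,000 runs per scenario agrees. At 0.3/0.3, coverage with both factors omitted is 98.1% instead of 95%, and the mean ICC is 0.095 against 0.049 with both included.

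**Case 2: strong baseline.** Assume a patient-level correlation and slope of 0.7 and a difference that is the same at baseline and follow-up. A 0.3 SD difference shrinks to 0.3 × (1 − 0.7) = 0.09. The residual SD is √(1 − 0.49) = 0.714, so 0.09/0.714 = 0.126 residual SD. With the same formulas and a residual ICC of 0.05:
- 0.3 SD for jurisdiction alone: a = (16/14) × 0.126²/4 = 0.0045; width ratio 1.007; ICC 0.054.
- 0.3 SD for both factors: a = 0.0091; width ratio 1.03; ICC 0.059.
- 0.2 SD for jurisdiction alone (0.084 residual SD): a = 0.0020; width ratio 0.99; ICC 0.052.

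A simulation with baseline adjustment, for 0.3 SD in jurisdiction alone, gave interval widths of 0.482 vs 0.476 (ratio 1.01) and ICC 0.054 vs 0.049.

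**Cost if neither factor matters.** 2.179/2.145 = 1.016, so intervals are about 1.6% wider with both factors included. With jurisdiction alone prognostic, break-even is a residual difference of 0.08 SD (ICC 0.01) to 0.13 SD (ICC 0.10).

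**The case against.** The strongest objection is that this argues from silence. The sentence describes a class of model and is not a closed covariate list. A journal article commonly leaves the fixed effects of an exploratory model to the full protocol or analysis plan, neither of which is shown. This stands to the extent that a reader might infer the models will exclude the allocation factors; the article does not say so. What remains is that the sentence says what the models handle and stops short of the design's own balancing factors, and adding them is cheap.

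Other objections:

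- **The harm is conditional.** A reader might infer that intervals are too wide and the ICC inflated whatever the outcome. The article quantifies no NI–ROI or size difference and calls the two populations broadly similar, and baseline adjustment can remove most of a stable difference. This stands and limits the point to outcomes weakly tied to baseline.
- **The planning ICC is not tied to these models.** Correct. An unadjusted ICC also suits a definitive analysis that does not adjust. The ICC is imprecise in any case: its large-sample standard error is about 0.95 × 1.95 × √(2/(20 × 19 × 15)) = 0.035, which exceeds the shift from 0.050 to 0.074.
- **Jurisdiction is not ignored.** Table 3 asks about NI–ROI differences across all process-evaluation domains, including effectiveness, and the economic analysis compares the settings. This stands, but neither puts jurisdiction into the arm-difference models.
- **Size and jurisdiction overlap.** NI practices are often larger, so an even split is idealised. A simulation with three large practices of eight in one jurisdiction and five of eight in the other still gave half-widths of 0.425 vs 0.341 and ICC 0.106 vs 0.051 at 0.3 SD for each factor, so the effect does not depend on the even split.
- **Inference is tentative.** The arm comparisons are exploratory, and the error is on the conservative side. This stands.

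**Conclusion.** The point holds as a conditional improvement. The named content of the models omits the factors that allocation balances. If those factors still predict outcome after baseline adjustment, arm-difference intervals are conservative and an ICC from the same model carries between-stratum differences.

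The size rests on assumptions the article does not supply: within-stratum ICC 0.05 and differences of 0.2–0.3 SD. For outcomes strongly correlated with baseline the effect is negligible to small (about 0–3% in interval width). For outcomes weakly tied to baseline, plausibly review completion and deprescribing because they concern events during follow-up, it is about 4–22%, with an ICC of about 0.06–0.096 instead of 0.05.

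The article contains no error or contradiction on this point. The feasibility outcomes and progression criteria do not use these models.

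**What to change.** 1. **Exploratory analysis:** state that the mixed model for each secondary outcome includes practice size (< 4 or 4+ GPs) and jurisdiction (NI or ROI) as fixed effects, with the baseline value where one exists and a practice random effect.
2. **Quantitative data collection and analysis, with a matching line in Sample size:** report the ICC and between-practice variance both with and without these two factors, and use for planning the one that matches the definitive trial's intended analysis.

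This changes wording only. Practice size is needed for minimisation and jurisdiction is known, so no new data are required. The statistical price is the two degrees of freedom costed above.

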The findings of the feasibility study justified proceeding to a randomised pilot trial to address remaining uncertainties and guide the decision to progress to a definitive trial of the intervention [16]. In particular, a pilot would allow testing of the MyComrade intervention and study procedures on a small scale [20] and inform important refinements to facilitate the conduct of a robust and transparent definitive trial [16, 21].

A funding opportunity arose for a pilot trial to be conducted across the Republic of Ireland-Northern Ireland border. This opportunity required that unique modifications would be made to the MyComrade intervention to account for the contextual differences in the Irish and Northern Irish health systems. The original MyComrade intervention, developed in the Republic of Ireland (ROI), included collaborative medication review by two GPs. In Northern Ireland (NI), the majority of primary care practices have access to a pharmacist, as a result of a Primary Care Pharmacy scheme launched in 2016 [22] ([name], personal communication, June 4, 2020), with a key responsibility for conducting medication reviews [23]. Therefore, the MyComrade collaborative medication reviews will take place in Northern Ireland with a GP and a practice-based pharmacist (PBP). Additionally, based on the findings of the feasibility study [16], the MyComrade intervention was further refined by adding a behaviour change technique (i.e. material incentive) to address the high opportunity cost of medication reviewing.

The aim of this study is to evaluate the feasibility of a trial of the modified MyComrade intervention, including cross-border comparison, using a pilot cluster randomised controlled trial (cRCT). The primary objective is to determine the feasibility of a definitive trial of the MyComrade intervention, focusing on recruitment, retention and fidelity of intervention implementation. The secondary objective is to select suitable outcome and cost-effectiveness measures for use in a definitive trial. This study will also enable the assessment of the feasibility of MyComrade in two different health systems, producing data on the adaptability and potential generalisability of the intervention.

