### Participants

#### Eligibility criteria

##### Primary care practices

Eligible practices in ROI will have at least two GPs willing to conduct medication reviews. In NI, at least one GP and one PBP must be willing to conduct medication reviews for a practice to be eligible. Practices currently involved in other research involving patients with multimorbidity will not be eligible.

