#### Health economic analysis

The health economic study will be conducted alongside the pilot cRCT to explore the feasibility of conducting an economic evaluation to assess the cost-effectiveness of the MyComrade intervention. Data collection tools will be developed for the purposes of collecting data on resource use and outcome measures over the trial follow-up period. An exploratory process will be conducted to identify the resource use and costs associated with the delivery of the intervention, in addition to the costs of clinical actions linked to the medication reviews, and other healthcare resource use by patients. Unit costs will be identified and applied to convert data on resource use to costs. For the pilot cost-utility analysis, quality-adjusted life-years (QALYs) will be generated using the EuroQol EQ-5D-5L [44]. A preliminary incremental analysis will be undertaken to provide information on the marginal costs and marginal effects of the MyComrade+ Intervention relative to the usual practice, and a range of techniques will be employed to address uncertainty. Preliminary subgroup analysis will compare data for the two different healthcare settings [45, 46]. This analysis is designed to determine the feasibility of this approach and not cost-effectiveness.

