## Discussion

This study will assess the feasibility of a trial of the MyComrade intervention by conducting a pilot cRCT of the intervention in the ROI and in NI. By bringing GPs/GPs and PBPs together, with supportive tools such as an organising checklist and allocated time, MyComrade aims to facilitate the sharing of expertise and experience to overcome the persistent barriers to medication management in primary care. This study will add to a growing body of research related to managing polypharmacy in primary care. Recent studies reflect the pressing need for evidence-based, comprehensive and feasible solutions that take into account the complexity of this issue and emphasise the needs and realities of the patient and primary care professionals and context [47, 48].

The introduction of PBPs in NI provides a unique opportunity to compare alternative approaches to enhancing medication reviews across different healthcare systems. The testing of this intervention in two different health systems (ROI and NI) will provide data on the adaptability and generalisability of the intervention. Although the populations of NI and ROI are broadly similar, self-reported health has been reported in one study to be lower in NI than in ROI—a feature that will warrant consideration in any future definitive cross-border trial of this intervention [26].

On completion of this study, the MyComrade intervention will have progressed through the development and feasibility/piloting phases of the MRC framework [16]. The development of interventions using a systematic approach such as that of the MRC framework is widely recommended to address persistent issues with study quality, effectiveness and implementation [49]. The theoretical basis for this intervention and specification of proposed mechanisms of impact enable a level of description and testing of the intervention that is now widely called for in intervention research [50]. Therefore, the findings of this study with respect to the pre-specified progression criteria and effectiveness outcomes will provide a strong indication of the appropriateness of moving to a full-scale trial.

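### The named arm comparison averages two different intervention-versus-usual-care contrasts, and NI–ROI differences cannot be attributed to pair type

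*Protocol article*

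**What the plan says.** **Pairing.** Trial design fixes the pair type by jurisdiction: "ROI pairs will be GP-GP, and NI pairs will be GP-PBP".

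**Comparator.** In the same section, "Control practices will proceed with usual care". The Introduction describes the NI pharmacist scheme as one "with a key responsibility for conducting medication reviews". Under Eligibility criteria, in NI "at least one GP and one PBP must be willing to conduct medication reviews for a practice to be eligible". Practices are randomised only after patients are recruited, so this criterion covers future NI controls as well. Study setting is more guarded: the pharmacist's tasks may include reviews, and hours and role vary by practice. No equivalent role is described for ROI.

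**Analysis.** The Introduction puts cross-border comparison within the study aim. For the secondary outcomes, Exploratory analysis names mixed-effects models that handle clustering and allow baseline adjustment, and one target: they "will be used to tentatively explore the differences in the secondary outcomes between the pilot trial arms". The economic section does name a split: "Preliminary subgroup analysis will compare data for the two different healthcare settings".

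**Use.** Under Sample size, "The estimates from this pilot trial will be used to calculate the sample size needed". The Outcomes section says the secondary outcomes will inform the definitive trial's primary outcome. The Discussion presents the NI pharmacists as an opportunity to "compare alternative approaches to enhancing medication reviews across different healthcare systems".

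**The concern.** Two things change together at the border: who delivers the intervention, and possibly what the controls receive. Medication review is both the behaviour that the intervention targets and a secondary outcome, so a difference in usual-care reviewing would act directly on a measured quantity.

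An arm difference taken over both jurisdictions mixes GP-GP review against ROI usual care with GP-pharmacist review against NI usual care. If those contrasts differ, their average describes neither health system. The control levels needed to choose an outcome and size a definitive trial would also be blended. A further risk lies in interpretation: the Discussion invites the reader to treat an NI–ROI difference as evidence about the two pairings, which the design cannot supply.

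**Working it through.** **1. The plan's own figure.** 16 practices × 20 patients = 320, as stated. There is no power calculation to reproduce.

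**2. What one arm difference estimates.** Let Δ_ROI and Δ_NI be the intervention-minus-control differences in each jurisdiction. With four practices per arm in each and equal practice sizes, the linear arm coefficient is

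Δ_pooled = (Δ_ROI + Δ_NI)/2,

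and it departs from each jurisdiction's value by |Δ_ROI − Δ_NI|/2. For example, 0.4 SD in ROI and 0.1 SD in NI give 0.25 SD.

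**3. Illustration for review completion.** The documents give no rates, so all rates here are assumptions: 80% completion in both intervention arms, 5–10% in ROI controls, 30–50% in NI controls.

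| Control ROI / NI | Δ_ROI | Δ_NI | Pooled | Departure from each |
|---|---|---|---|---|
| 10% / 30% | 70 | 50 | 60 | 10 |
| 5% / 30% | 75 | 50 | 62.5 | 12.5 |
| 10% / 50% | 70 | 30 | 50 | 20 |
| 5% / 50% | 75 | 30 | 52.5 | 22.5 |

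Contrasts are in percentage points. With equal completion in both intervention arms, the departure is half the gap in control rates; if the gap is zero, it vanishes.

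**4. Can pair type be separated?** Take 16 practices with columns for intercept, NI, arm and arm × NI. The rank is 4 of 4, so both within-jurisdiction differences, and the gap between them, are estimable. An indicator for GP-pharmacist pairs equals arm × NI exactly, so adding it gives five columns and still rank 4. The gap is

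Δ_NI − Δ_ROI = (GP-pharmacist in NI − NI usual care) − (GP-GP in ROI − ROI usual care),

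which contains pair type, usual care and every other difference between the systems.

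**5. Precision of a split.** The variance of a practice mean in SD units is v = ICC + (1 − ICC)/20. The standard errors are √(v × 2/8) pooled, √(v × 2/4) within a jurisdiction, and √2 times the latter for the gap. Degrees of freedom are 16 − 3 = 13, 8 − 2 = 6 and 16 − 4 = 12. No ICC is given, so the values below are assumptions. Entries are 95% interval half-widths in SD units.

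| ICC | Pooled, 8 v 8 | One jurisdiction, 4 v 4 | Gap between jurisdictions |
|---|---|---|---|
| 0.01 | 0.26 | 0.42 | 0.53 |
| 0.05 | 0.34 | 0.54 | 0.68 |
| 0.10 | 0.41 | 0.66 | 0.83 |

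**6. Dependence on the 4:4 split.** Trial design gives four practices per arm in each jurisdiction, but Randomisation lists only practice size as a minimisation factor. If the split were not enforced, an unrestricted 8:8 allocation would produce it with probability (70 × 70)/12870 = 4900/12870 = 0.38. Otherwise an arm difference without a jurisdiction term would also carry the difference in level between jurisdictions.

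**The case against.** The case on the other side is substantial.

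- **Silence is not pooling.** Exploratory analysis is one sentence in a condensed article. Model terms are usually left to an analysis plan, which is not shown and may include jurisdiction. This stands, and the absence of a covariate list is not itself an error.
- **A reader might infer that neither contrast is estimated.** The documents do not support that. The randomised arm difference is estimable as an average, and for a cross-border trial that average can be a legitimate target. The within-jurisdiction differences are estimable too; they are simply not named.
- **A reader might infer that NI usual care definitely contains pharmacist reviews.** Study setting says only that it may. ROI eligibility also requires two GPs willing to review. Table 3 asks whether pairs completed reviews, so reviews by a pharmacist alone might not count. Hence the gap could be small or nil.
- **A reader might infer that only the economic analysis looks at setting.** Table 3 also asks about NI–ROI differences in experience across all domains, and asks control practices about usual care. This stands. However, the sources listed for the cross-border question are interviews and a practice profile questionnaire, which do not give control-arm outcome levels by jurisdiction.
- **The Discussion promises little.** It speaks of an opportunity, and of adaptability and generalisability. That is fair, but the sentence still invites a comparison of approaches, and no analysis plan can remove the aliasing.
- **Little turns on it.** The arm comparison is tentative, progression uses no arm differences, and the quantitative section stresses variability, missingness and the ICC. This limits the weight of the point. It does not remove the need for planning inputs that match each health system.

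**Conclusion.** The point holds in a limited form. Pair type is completely aliased with jurisdiction; this is a fact of the design and needs no assumption. Usual care may differ by jurisdiction, since every NI practice in both arms has a pharmacist willing to review. The only secondary-outcome contrast named is between arms. Given the stated 4:4 allocation, it averages two different intervention-versus-usual-care contrasts, although cross-border comparison is part of the aim and the economic analysis is split by setting.

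The size of any usual-care gap is unknown from the documents. The 10 to 22.5 points above rest wholly on assumed rates and show how the average behaves; they do not predict what will be seen. The consequence falls on outcome choice and on inputs to the definitive trial. The primary feasibility outcomes and progression criteria are untouched.

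**What to change.** 1. **Exploratory analysis.** Include jurisdiction in the models. Keep the pooled arm difference and, beside it, report for each secondary outcome the control-arm level and the intervention–control difference in NI and in ROI, with intervals, labelled descriptive.
2. **Sample size and Quantitative data collection and analysis.** Carry jurisdiction-specific control levels and variability into the sizing work. Including jurisdiction also keeps a difference in level between the two systems out of the between-practice variance from which the ICC is estimated.
3. **Discussion.** State that each version is compared with usual care in its own health system, and that NI–ROI differences cannot be attributed to pair type.

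The cost is some wording and an additional model term, with no data beyond those already planned. The downside is imprecision: at an assumed ICC of 0.05, the half-width grows from 0.34 SD pooled to 0.54 SD within a jurisdiction. For that reason the split should accompany the pooled estimate and not replace it.
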